### Recruitment

Potential participants recruited from NHS providers (through routine appointments or via phone or letter contact) will be invited to complete a ‘permission to contact’ form that includes information about the study and gives agreement for the research team to contact the individual. Within GP practices electronic case records will be searched by a member of practice staff, using appropriate read codes followed by case note search as needed, and eligible patients will be sent the permission to contact form.

The study will also be advertised more widely to encourage self-referral, including through lists of people interested in research held by the University of Exeter and University of Lancaster, posters in public areas, social and traditional media, and promotions by relevant charities.

Following an expression of interest, patients referred by a secondary care clinician will be sent full study information and invited to attend a baseline assessment interview in person. Those not referred by a secondary care clinician, and thus who may not have had a comprehensive mental health assessment prior to referral, will first be invited to undergo a telephone screening call with a member of the research team, after giving consent for this step of the study. At the baseline assessment interview researchers will take written informed consent, confirm eligibility and collect baseline measures, some of which will be completed by participants in their own time after the interview. Eligible, fully informed and consenting participants will then be entered into the study.

### Trial interventions

The ThrIVe-B programme has been developed iteratively in consultation with ThrIVe-B patients and others with personal experience of BDs. It follows five key principles of DBT: (1) clearly structured treatment; (2) application of behavioural therapy; (3) emphasis on validation of emotional response; (4) dialectical stance, balancing acceptance and change; and (5) integration of mindfulness practice. Topics covered include skills for observing events, thoughts, emotions and bipolar symptoms without reacting impulsively; balancing lifestyle and activities to maximise mood stability and healthy rather than hypomanic positive mood; and skills for down-regulating emotion, problem-solving and negotiating interpersonal difficulties (which are often a consequence and a trigger of bipolar mood swings). As is standard DBT practice ThrIVe-B emphasises the importance of participants learning skills through teaching and practice, having opportunities to generalise these skills across real-world contexts, and continuing use of skills beyond treatment end. This will be achieved structurally through a combination of group meetings (15, held weekly) and up to 8 concurrent fortnightly individual sessions of up to 45 min delivered in person or by telephone.

To enhance real-life generalisation of skills, participants in the ThrIVe-B arm will be given a custom-built smartphone application (‘app’) which alerts participants to rate their mood level at random points each day (number of daily alerts determined by user). Handsets can be borrowed by participants without their own. When mood is above or below user-determined ‘high’ and ‘low’ mood thresholds, a feedback screen appears containing advice pre-entered by the user, which can include skills learned in the ThrIVe-B programme. A version of this app, with reduced functionality, will be used to monitor mood variability in real time over 7-day periods at baseline and at follow-up for all participants.

In addition there will be an optional supporters’ group meeting (midway through the series of group meetings) during which friends or relatives can attend and learn about the skills covered, enabling them to better support the participant with use of these. To support the generalisation and ongoing adoption of skills beyond the acute treatment, patients will be invited to attend a group ‘reunion’ booster session at 3 months after therapy.

ThrIVe-B therapists will be psychological therapists with a background in either cognitive behavioural therapy or DBT. Training for the ThrIVe-B programme will be a 5-day course. Assuming participants’ consent, therapy sessions will be taped and recordings used to develop fidelity and competency measures for use in a definitive trial. Recordings will also be used to inform weekly supervision sessions during the active treatment phase. Participants will complete the Beck Depression Inventory [25] and Altman Scale for Rating Mania [26] prior to each group session, and the scores will be used to inform their care, as well as forming part of the research data collected.

Our comparison arm is ‘usual care’. This is because there is currently no gold standard psychological treatment for this client group against which to benchmark a new treatment. There are no formal data to indicate the likely content of TAU for individuals with BPMI across the United Kingdom; thus, we will record this in terms of the services received by each participant during the trial in order to characterise the variability of TAU within and between study sites, based upon responses to the resource use questionnaire. No restrictions will be placed on the content of TAU, other than the study entry criterion which excludes individuals currently receiving psychological therapy for BD.

### Outcomes

We will conduct follow-up assessments at 3, 6, 9 and 15 months after baseline, with the 3- and 6-month assessments being conducted via post or online, and the 9- and 15-month assessments including a face-to-face or telephone interview.

#### Primary outcome measures

Feasibility will be assessed in terms of numbers of patients identified, approached, consented, randomised and completed over the active period of recruitment and treatment, as well as participant attrition from the trial and from treatment. As part of feasibility and acceptability analyses we will assess whether the continuation rules stated previously have been met.

To assess acceptability all participants will complete a questionnaire about their experience in the trial, including ranking candidate primary outcome measures at 9-month follow-up in terms of their perceived personal value and relevance, and a subset of 12 participants will be invited to take part in a semi-structured interview to allow more detailed exploration of their experiences of both the research study and the treatment. Sampling will be purposive and will include participants from across the two trial arms and trial sites to facilitate understanding of the potential impact of differential therapy and trial contexts. It will also seek to include individuals who did, and who did not, complete treatment and study assessments. Participants who exit the study at any point in the process will be invited to complete a brief survey of their reasons for exiting, and experiences of the trial so far.

As part of the study, referring clinicians will be asked to take part in the process evaluation, giving their views of the therapy and research process via a brief survey form. In addition, ThrIVe-B therapists will be invited to take part in an interview asking about their experiences and views of the therapy and associated training following the end of their involvement in the intervention phase. Patient adherence to treatment will be indexed by the number of therapy sessions attended.

#### Secondary outcome measures

Participants will complete the following measures at baseline and all follow-up points, representing candidate primary outcome measures for a future definitive trial: the Patient Health Questionnaire 9-item scale [27], which measures depressive symptoms; the ALS [28]; the Bipolar Disorder Recovery Questionnaire [29]; and the Quality of Life in Bipolar Disorder scale [30]. Participants will also complete the Generalised Anxiety Disorder 7-item scale [31]. At baseline, 9 and 15 months, the Bech Mania Rating Scale [32], the Hamilton Depression Rating Scale [33] (both observer-rated), and the Brief Adherence Rating Scale for medication adherence [34] will be completed, as will relevant sections of the Structured Clinical Interview for DSM-V [35] to assess both eligibility criteria, and presence of affective episodes during the follow-up period.

In addition, participants will complete the EuroQoL 5-dimension 5-level (EQ-5D-5L) instrument [36] and the 36-item Short Form Health Survey [37] in order to assess how feasible it is to use these measures in this population. This will allow us to identify potential reasons for incomplete data. In the future randomised controlled trial, the scores will be used to obtain utility values for deriving quality-adjusted life-years in order to estimate incremental cost-effectiveness ratio. Participants will be asked also to complete a resource use questionnaire (last 6 months or since last assessment point) to assess the feasibility of collecting health and social service use. Information on the resource use and costs of delivering the ThrIVe-B programme will be collected.

#### Quantitative process measurement

To inform process measurement in a definitive trial, measures of hypothesised mechanisms of change will be included, providing data on their performance and acceptability to participants. Hypothesised treatment targets include mood-related impulsivity, avoidance and interpersonal functioning (Positive and Negative Urgency, Premeditation, Perseverance, Sensation-Seeking impulsive behaviour scales [38]; Behavioral Activation in Depression Scale [39]), emotional acceptance and mindfulness skills (Kentucky Inventory of Mindfulness Skills [40]), emotional problem solving (Means-Ends Problem Solving task [41]) and social rhythm stability (adapted Social Rhythm Metric [42]).

#### Experience sampling

Experience sampling will be carried out using the purpose-built ThrIVe-B app to gather data on mood variability in real time. This is a potential secondary outcome in a definitive trial; therefore, in the current trial we wish to test the feasibility and acceptability of gathering these data within both arms of the trial, assessed by return rates and participant feedback. Participants will be invited to use the app for 1 week at baseline and at 9-month follow-up. In addition, the app, with additional functionality enabled, will be used by those in the ThrIVe-B + TAU arm as part of treatment, as described previously. In order that those in the TAU arm rate over a period similar to that in the ThrIVe-B arm, and in order that mood variability data are available from both groups over the treatment period of the study, those in the TAU arm will be prompted to use the app at month 3, until month 9. The version they use will not contain the therapeutic elements (namely specifying a threshold and pre-programming feedback); instead they will simply be able to select the number of mood rating alerts per day and rate mood.

#### Participant ranking of outcome measures

In order to gather information on patient-valued outcomes at the 9-month follow-up point, participants will be asked to rank measures to reflect their personal priorities with respect to areas in which they would want to see change following a treatment: depression symptoms, anxiety symptoms, mood changes, sense of personal recovery and quality of life.

### Procedure

Following the initial eligibility assessment and completion of baseline measures, including 7 days of experience sampling using the app, participants will be invited to complete follow-up assessments at 3, 6, 9 and 15 months after baseline, with an additional 7 days of experience sampling at the 9-month point. Assessments will be in person (face to face or by telephone), by post or online, dependent upon patient preference, with in-person contact required at months 9 and 15 in order to complete the interview-based measures. Figure 1 (SPIRIT figure) displays the measures completed at each time point.

**Fig. 1 Fig1:**
[figure not shown]
Schedule of enrolment, interventions and assessments (displayed according to Standard Protocol Items: Recommendations for Interventional Trials [SPIRIT] template)

At month 9, in addition to completing the set of measures, participants will be asked to rank them. Also at month 9, a subset of participants will be invited to take part in a semi-structured interview about their experiences of the trial with an unblinded member of the research team.

### Data analysis

#### Quantitative data analysis

Patients’ demographic characteristics at baseline will be reported by treatment group. The primary analyses will be performed after 9-month follow-up and after data cleaning is completed and the database finalised. Further analyses will be performed after the final 15-month follow-up. No interim analyses are planned.

All analyses will be done on an intention-to-treat basis; included outcomes will be reported according to randomised allocation and regardless of the treatment actually received. There will be no possibility of participants allocated to the control arm receiving the intervention; it is possible that participants allocated to the intervention will in actuality receive none of the intervention or will not complete the intervention (defined as attendance of at least 50% of group sessions). All outcomes will be reported descriptively. At 9-month follow-up only, an inferential analysis will be performed for continuous outcomes only, reporting the relevant 95% CI for the between-group mean difference (intervention minus TAU), but no *p* value. Inferential analyses will include the randomisation covariates: site and baseline medication status. No interactions between intervention status and covariates are planned.

Proportions of participants recruited (of those approached) and those lost to follow-up at 3, 6, 9 and 15 months, will be reported with 95% CIs. All analyses will use complete case data only. No attempts to address missing data, such as multiple imputation, will be made.

The economic analysis will take the NHS and social care perspective. No covariate analysis or subanalysis will be conducted, because this is a feasibility trial and is not powered for such inferential analyses. Descriptive data for each arm will be reported with CIs for between-group comparisons. No *p* values will be reported.

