### Objectives

We have the following objectives in this trial:To establish recruitment pathways and trial teams in two trial sitesTo inform the recruitment and timeline of a future fully powered trial by establishing the number of participants initially identified, approached, consented, randomised and completedTo refine future trial procedures by establishing the acceptability and experience of the trial process to participants, including randomisation and completion of outcome measuresTo further assess the acceptability of the treatment via qualitative interviews and, based on input from trial participants and clinicians, to further refine and develop the treatment manual and the procedures for training, supervising and assessing the competence of trial therapistsTo determine the optimal primary outcome measure in a future trial by assessing the performance of selected candidate primary outcome measures with respect to level of acceptability to participants (completion rates, perceived burden) and participant-perceived relevance and valueTo inform estimation of sample size for a future trial by measuring data completeness at follow-up (participant attrition), SD of the likely primary outcome measure, and the variability of the comparator condition, treatment as usual (TAU), across individuals and sitesTo pilot a measure of resource use and to assess the feasibility and acceptability of candidate health economics measures to inform the future definitive trialTo identify, measure and cost the resources needed to deliver the intervention

We will also evaluate whether the following continuation criteria have been met prior to planning a future definitive trial:Trial participation does not lead to serious negative consequences (unexpected serious adverse reaction) for our participants.Any serious concerns about the acceptability and feasibility of the trial procedures can be rectified prior to a full trial.Follow-up data at 9 months are available for at least 60% of participants.At least 60% of patients in the intervention group complete treatment (attend at least 50% of possible sessions).

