### Design

We will conduct a feasibility study with a two–arm, randomised, parallel, controlled trial design. Participants will be randomised in a 1:1 ratio to TAU only (control arm) or TAU plus the ThrIVe-B programme (intervention arm). Outcome measures will be recorded at baseline and at four follow-up points—3, 6, 9 and 15 months after randomisation—with 9 months as the primary end point and the point of qualitative interview (because all participants will have completed treatment by this point).

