### Sample size

A total of 48 participants (24 per group) will allow us to address the stated objectives of this feasibility trial. This represents recruitment to three ThrIVe-B groups at full capacity (8 per group), with equivalent numbers randomised to TAU. On the basis of our previous work on the ThrIVe-B programme, we estimate an attrition rate of 17% with respect to the primary end point at 9 months post-randomisation. Our sample size of 48 will allow us to estimate this level of attrition for a future definitive trial with a precision of ±15% with 95% certainty and allow us to estimate the SDs for any potential primary outcome measures that would inform the power calculation for a definitive trial.

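### Treatment is given in three therapy groups of eight, but neither the 9-month confidence intervals nor the inputs to the definitive sample size make any stated allowance for therapy-group clustering

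*Protocol article*

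**What the plan says.** The Sample size section derives the total from the delivery format: "This represents recruitment to three ThrIVe-B groups at full capacity (8 per group), with equivalent numbers randomised to TAU". Trial interventions describes 15 weekly group meetings plus up to eight individual sessions. TAU has no group structure.

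Under Quantitative data analysis, continuous outcomes at 9 months get an inferential analysis "reporting the relevant 95% CI for the between-group mean difference (intervention minus TAU", without a p value. The analysis is to include site and baseline medication status. Interactions between intervention and covariates are not planned, and complete cases only are used. Therapy group is not named.

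The Objectives section lists what the trial will measure to inform the future sample size: attrition, then "SD of the likely primary outcome measure, and the variability of the comparator condition", the last of these across individuals and sites. Variation between therapy groups is not on the list.

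**The concern.** Members of one therapy group share its sessions and each other's company for 15 weeks, so their outcomes may be correlated. TAU participants have no such shared exposure. The design is therefore partially nested, with clustering in one arm only. If the correlation is positive and the analysis has no term or correction for it, the SE of the mean difference is too small and the 95% interval covers less than 95%.

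The second consequence is for planning. Informing the definitive sample size is a stated objective. The list provides for variability in the ungrouped arm but not for between-group variability in the arm where treatment is given in groups.

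**Working it through.** **Inputs from the protocol article.** 48 participants, 24 per arm, 1:1; three groups of eight in the intervention arm (Sample size); two sites (Setting and participants); 17% expected attrition at 9 months (Sample size). The stated total reproduces: 3 × 8 × 2 = 48.

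**Assumed input.** The therapy-group ICC, which the documents do not give: 0.01, 0.05 and 0.10. The two arms are taken to have equal total variance.

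**Does the site term deal with it?** No. Three groups over two sites means that at least one site holds two or more groups, and a site effect cannot separate groups within a site. The site effect is also common to both arms, whereas the clustering is in one arm, and no intervention-by-site interaction is planned.

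**Effect on the SE.** The intervention-arm design effect is DE = 1 + (m − 1) × ICC. The variance of the difference is multiplied by (DE + 1)/2 and the SE by its square root. Coverage of an uncorrected interval is obtained by dividing the t quantile (44 df = 48 − 4 parameters at full follow-up) by the SE ratio.

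| ICC | DE, m = 8 | Variance ratio | SE ratio | Coverage | SE ratio, m ≈ 6.6 |
|---|---|---|---|---|---|
| 0.01 | 1.07 | 1.035 | 1.017 | 94.6% | 1.014 |
| 0.05 | 1.35 | 1.175 | 1.084 | 93.0% | 1.068 |
| 0.10 | 1.70 | 1.350 | 1.162 | 91.0% | 1.132 |

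The last column uses 8 × 0.83 = 6.64 per group, because the analysis is complete-case and the protocol says "we estimate an attrition rate of 17% with respect to the primary end point at 9 months post-randomisation".

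**Width of the interval, in SD units.** At full follow-up the uncorrected half-width is t(44 df) × √(2/24) = 0.58. With the variance inflated it is 0.63 at ICC 0.05 and 0.68 at ICC 0.10. With Satterthwaite degrees of freedom for three clusters (about 5.8 and 4.9) it is 0.77 and 0.87. Most of that further widening comes from having only three groups: the same method gives 0.68 even at ICC 0.

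**Effect on a definitive total.** For groups of eight and 1:1 allocation, the total is multiplied by the variance ratio, so 3.5% / 17.5% / 35% more participants are needed. As an illustration with an assumed effect of 0.4 SD and 90% power, 264 becomes 264 × 1.035 ≈ 274, 264 × 1.175 ≈ 311 and 264 × 1.35 ≈ 357.

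**Can this trial estimate the ICC?** Not usefully. With three groups of eight and a point estimate of 0.05, F = 1 + 8 × 0.05/0.95 = 1.42, and the 95% interval for the ICC runs from about −0.09 to 0.87.

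**The case against.** A reader might infer that the plan treats all participants as independent. The article does not say so. It says that site and medication status will be included, not that nothing else will be, and it names no model type. A group term could sit in the full protocol or the statistical analysis plan, neither of which is shown. This stands, and it limits the point to the terms and inputs that the article names.

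A reader might also infer that the definitive trial will be undersized. That does not follow either. No definitive total or formula is fixed, the list of inputs is not called complete, and planners can take an ICC from elsewhere. Given how poorly three groups estimate it, leaving the ICC off a list of quantities to be measured here is defensible. Leaving group correlation out of the planning inputs altogether is harder to defend.

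The size depends on an assumed ICC. At 0.01 it is under 2% of the SE, and with expected attrition the figures fall to about 1% / 7% / 13%. The primary outcomes are feasibility and acceptability, and none of the four continuation criteria uses the mean-difference interval. All of this stands.

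It does not remove the point. The article goes far enough to name adjustment terms and planning inputs, and both omit a dependence that the sample size is itself built on.

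**Conclusion.** The point holds in a limited form. As written, the plan makes no stated allowance for therapy-group clustering in the 9-month intervals or in the inputs to the definitive sample size, and the site term does not provide one. If the ICC is positive and nothing is added, the intervals are too narrow: by about 8% of the SE at an assumed ICC of 0.05 and 16% at 0.10 with eight per group, somewhat less after attrition, and negligibly at 0.01. Expressed as a share of the total required, a definitive trial that ignored the ICC would fall short by 3.5/103.5 = 3%, 17.5/117.5 = 15% or 35/135 = 26%.

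These sizes rest on the assumed ICCs, groups of eight and equal variances. The feasibility conclusions of this trial are not affected. It is worth correcting because the interval is the planned inferential result for continuous outcomes, and because sizing the next trial is one of this trial's purposes.

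**What to change.** - **Quantitative data analysis:** keep the planned interval. Beside it, report intervals with the intervention-arm variance inflated for an assumed therapy-group ICC, for example 0, 0.05 and 0.10, using the number analysed per group. A partially nested model, with a random group effect in the intervention arm only, can serve instead, but only as a sensitivity analysis, because three groups cannot support it as the main one.
- **Objectives, sample-size inputs:** add therapy-group size and an ICC range taken from external sources. Do not rely on an ICC estimated from this trial.
- If the statistical analysis plan already has a group term, state it in both documents so that they agree.

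The cost is a little more analysis and wider reported intervals. At full follow-up the half-width goes from 0.58 SD to 0.63 or 0.68 SD with assumed ICCs of 0.05 or 0.10, and to about 0.77 or 0.87 SD with small-sample degrees of freedom for three groups. No extra participants or outcome measures are needed; the analysis needs only a record of each participant's therapy group.

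### The 9-month between-arm model names site and medication status as covariates but not the outcome's own baseline score, so its confidence intervals are probably wider than the collected data allow

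*Protocol article*

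**What the plan says.** The protocol article, under Quantitative data analysis, plans a between-arm inferential analysis of continuous outcomes at 9 months only. It takes the form of a 95% confidence interval for the mean difference, without a p value. On the model it says "Inferential analyses will include the randomisation covariates: site and baseline medication status" and "No interactions between intervention status and covariates are planned". On missing data it says "All analyses will use complete case data only".

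No section mentions the outcome's baseline value as a covariate, a change score or a repeated-measures model. The statement in the same section that rules out covariate analysis stands in the paragraph on the economic analysis and does not govern this model.

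The baseline scores will exist. The section on secondary outcomes says so for the self-report measures: "Participants will complete the following measures at baseline and all follow-up points, representing candidate primary outcome measures for a future definitive trial". The observer-rated scales are also covered: "At baseline, 9 and 15 months, the Bech Mania Rating Scale" and the Hamilton Depression Rating Scale are scheduled together.

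Under Randomisation, concealment of allocation, and blinding, the minimisation factors are site and medication status, and the first ten participants are allocated by simple randomisation. Under Objectives, one aim is to inform the later sample size through the "SD of the likely primary outcome measure, and the variability of the comparator condition".

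**The concern.** A participant's baseline score is often a useful predictor of the same score at follow-up. Leaving it out of the model keeps in the error term variation that could be explained at almost no cost. Neither the allocation method nor the named covariates deal with baseline severity. In a trial with about 20 analysed per arm, the arms can differ noticeably at baseline by chance, and part of that difference passes into the 9-month contrast.

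What is at stake is the precision of the clinical effect intervals and how they can be read if the arms turn out to be unbalanced. There is a second, smaller matter. The trial is meant to supply inputs for sizing a definitive trial, and the baseline-to-9-month correlation would be a useful one, but the article does not say it will be reported.

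**Working it through.** **Inputs from the protocol article.** 48 randomised, 24 per arm, and 17% expected attrition at 9 months (Sample size). 48 × 0.83 = 39.8, so about 40 analysed, or 20 per arm. The article states no SD, effect size, correlation or precision for this interval, so there is no figure of its own to reproduce on this point.

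**Assumption.** ρ is the within-arm correlation between baseline and 9-month score, taken as 0 to 0.7. Results are in units of the outcome SD, with site and medication status treated as explaining little of the outcome.

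**Half-width with site and medication only.** Four parameters, so df = 2 × 20 − 4 = 36:

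t(36) × √(2/20) = 2.028 × 0.316 = 0.64 SD.

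**Half-width with the baseline score added.** Five parameters, so df = 35. The last factor is the average cost of estimating the extra slope:

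t(35) × √(2/20) × √(1 − ρ²) × √(1 + 1/34) = 2.030 × 0.316 × √(1 − ρ²) × 1.015.

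| ρ | Half-width (SD) | Ratio to model without baseline score | Equivalent sample-size factor (1/ratio²) |
|---|---|---|---|
| 0 | 0.65 | 1.016 | 0.97 |
| 0.2 | 0.64 | 0.995 | 1.01 |
| 0.3 | 0.62 | 0.969 | 1.07 |
| 0.5 | 0.56 | 0.880 | 1.29 |
| 0.7 | 0.47 | 0.725 | 1.90 |

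The ratios hardly depend on the number analysed. At ρ = 0.3, 0.5 and 0.7 they are 0.966, 0.877 and 0.723 with 24 per arm (no attrition). With 15 per arm, close to the 60% follow-up threshold (48 × 0.6 = 28.8 in total), they are 0.976, 0.886 and 0.730.

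**Simulation check.** 6,000 replicates per ρ were run with 20 per arm, normal scores and two binary covariates. The ratios were 1.02, 0.97, 0.88 and 0.73 at ρ = 0, 0.3, 0.5 and 0.7, in agreement with the formula.

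**Chance imbalance.** The SD of the baseline mean difference is √(2/20) = 0.316 SD. The probability that it exceeds 0.3 SD in either direction is 2 × [1 − Φ(0.3/0.316)] = 0.34. With equal SDs at both times, a 0.3 SD imbalance moves the contrast that ignores baseline by ρ × 0.3, which is 0.09, 0.15 or 0.21 SD at ρ = 0.3, 0.5 or 0.7.

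**Coverage.** Without the baseline score, simulated coverage was about 95% over all replicates at every ρ. In the 11–12% of replicates with imbalance above 0.5 SD it was 91%, 88% and 80% at ρ = 0.3, 0.5 and 0.7. With the baseline score it stayed at 94–96% in those same replicates.

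**The case against.** **The wording is inclusive.** The sentence does not say that nothing else will enter the model. This is a condensed article, and an analysis plan not shown here could add the baseline score. That is a fair caution about certainty. But the article does name a covariate set and rules out interactions, so an analyst who follows the text as written would leave the baseline score out.

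**No decision rests on the interval.** This stands. The four continuation criteria under Objectives concern safety, rectifiable concerns, 60% follow-up and 60% treatment completion. A reader might also infer that this interval is the trial's only inferential result. It is not: the article plans confidence intervals for recruitment and loss-to-follow-up proportions and for the economic comparisons as well.

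**The gain may be small.** This stands in part. Nine months separate the two scores, participants are selected for fluctuating mood, and those in an acute episode are excluded. A low correlation on some scales is therefore plausible, and at 0.3 the gain is only about 3%. The downside at zero correlation, about 1.6%, is smaller still.

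**The definitive trial would not be mis-sized.** A reader might infer that the plan passes on the wrong SD. The documents do not say how the later trial will be analysed, and a raw SD is a legitimate, conservative input. The correlation can also be computed from the collected data whichever model is fitted.

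**Adjustment may cost participants.** This stands. Under Recruitment, some baseline measures are completed by participants in their own time after the interview. With complete-case analysis, anyone missing the baseline score would drop out of that model.

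**Conclusion.** The point holds as a question of efficiency. The stated covariates omit a baseline score that is already collected and that neither minimisation nor the model otherwise accounts for. With about 20 analysed per arm, including it would narrow the 9-month intervals by about 3%, 12% or 27% at correlations of 0.3, 0.5 or 0.7. Nothing is gained near 0.2, and the interval is about 1.6% wider at zero. These correlations are assumptions, and the calculation takes equal arms and complete baseline scores among those analysed.

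A reader might infer that the planned interval is biased or invalid. It is not. Over repeated randomisations it is unbiased, with about 95% coverage, and the weakness appears only conditionally, when the arms obtained happen to differ at baseline. The point is worth correcting because the change is cheap, but it does not threaten the feasibility conclusions.

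**What to change.** Reword the covariate sentence along these lines: *the 9-month models will adjust for site, medication status at baseline and the baseline value of the outcome being analysed.* For each candidate primary outcome, report the baseline-to-9-month correlation, or the residual SD, next to the raw SD, so that the definitive trial can be sized under either form of analysis.

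The cost is one degree of freedom per model and no new data collection. Because analysis is complete-case, any participant without the relevant baseline score would be lost from that model, so the number analysed should be reported for each outcome and baseline questionnaires completed after the interview should be followed up.
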